## Abstract

**Background:**

Gestational diabetes is a type of carbohydrate intolerance that is diagnosed for the first time during pregnancy. Researches have shown that gestational diabetes is associated with many negative prenatal and birth outcomes. Because of the complications such as infant death, several diabetics’ mothers plan to stop breastfeeding. Research findings indicate a decrease in breastfeeding in mothers with gestational diabetes/ or contradictory tissues regarding the factors affecting the breastfeeding behavior of mothers with gestational diabetes and a special program to promote breastfeeding for these mothers based on the social and cultural conditions of Iranian society. The present study aims to design an interventional program with a mixed qualitative study based on the theory of planned behavior (PBT) to prevent the decrease of breastfeeding in diabetic mothers.

**Methods/design:**

A mixed methods exploratory design will be used to conduct this study in 3 phases. The first phase (qualitative): The purpose of the first phase is to understand the experience of breastfeeding mothers who had gestational diabetes, which will be done using the directed content analysis method. The purposive sampling will be used on pregnant mothers with gestational diabetes 30–34 weeks and mothers with infants (up to 6 months) with a history of gestational diabetes. The second phase include designing and implementing an educational program based on the PBT: Education will be conducted based on the needs assessment of the qualitative phase, the opinions of the focus group, and the literature review, then the breastfeeding behavior will be measured using the survey tool of “breastfeeding drop”. The third phase: Interventional quantitative phase: The sample size will be carried out by a pilot study, then a designed program as an educational intervention for teaching breastfeeding behavior based on the PBT for 30–34 weeks pregnant mothers with gestational diabetes will be implemented during 3–4 sessions and breastfeeding behavior will be evaluated after delivery.

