This shows the necessity of investigating the experiences of mothers with gestational diabetes from breastfeeding in different sociocultural contexts. The result of Negvin. et al. study (2019) showed that the risk of early cessation of breastfeeding 12 months after delivery is higher in mothers with gestational diabetes, Also they conducted a one-year prospective study on 2030 Vietnamese mothers with gestational diabetes to investigate the relationship between gestational diabetes and the length of breastfeeding after giving birth. They reported that the relative risk of stopping breastfeeding in mothers with gestational diabetes was much higher compared to healthy mothers who were examined in the first, third, sixth, and 12th months after delivery [5]. The result of Herbert et al. study (2021) showed that gestational diabetes was more common in American Indian, Alaska Natives, and Hispanic women than in black and non-Hispanic women (12% vs. 9%), and those with gestational diabetes had the lowest rates of exclusive breastfeeding (51% vs. 57–69%) compared to other women without gestational diabetes [4]. The results of many studies showed that stopping breastfeeding early was associated with many complications for the mother and the baby [6–18]. The results of Chertok et al. study (2016) showed that there is a relationship between breastfeeding self-efficacy and the breastfeeding behavior of mothers. They showed that breastfeeding self-efficacy can be increased by encouraging and supporting breastfeeding by health care providers and facilitating early and continuous breastfeeding. Early breastfeeding support is important among women who are at increased risk for delayed initiation of lactation or delayed lactogenesis II, such as women with gestational diabetes [19]. The results of qualitative studies showed that women with diabetes emphasized the need for continuous counseling about breastfeeding and education as well as help to solve breastfeeding challenges [20, 21]. Considering the incomparable benefits of breastfeeding for both mother and baby, management and follow-up of breastfeeding for mothers with gestational diabetes should be one of the basic challenges for every society. Women with gestational diabetes need ongoing support after hospital discharge to maintain long-term breastfeeding [5].

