### Study aim

By achieving the results of this study, it is possible to get a deep insights and detailed information about the understanding of diabetic mothers about maintaining breastfeeding according to their needs and expectations, as a result, to explain the breastfeeding experience of mothers with gestational diabetes and to design and implement an educational program and evaluate the its’ effects on mothers’ breastfeeding behavior after delivery.

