### Specific objectives of the qualitative stage

Explanation of breastfeeding behavior of women with gestational diabetesExplaining the perceived behavioral beliefs of women with gestational diabetes about breastfeeding behaviorExplaining the perceived subjective norms of women with gestational diabetes about breastfeeding behaviorExplanation of perceived control beliefs of women with gestational diabetes from breastfeeding behaviorExplaining the behavioral intention of women with gestational diabetes regarding breastfeeding

The general goal of the second quantitative stage: designing an educational program based on the theory of planned behavior.

Specific Objectives of the second phase of educational program design:Assessment and prioritization of the educational needs of women with gestational diabetesDetermining the goals and activities of the educational program for women with gestational diabetes.Evaluation design of educational program designed for women with gestational diabetes

The overall goal of the third quantitative phase: determine the effect of the implementation of the educational program based on the theory of planned behavior on the breastfeeding behavior of women with gestational diabetes.

The specific objectives of the third phase are to determine the effectiveness of the implementation of the educational program: which will be measured based on the “breastfeeding drop prediction tool”.Determining the comparison of breastfeeding behavior of women with gestational diabetes before and after the implementation of the interventionDetermining the comparison of breastfeeding intention of women with gestational diabetes before and after the implementation of the intervention

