### Research population

Mothers with a history of gestational diabetes and infants up to one year are covered by comprehensive health centers, and also who are eligible for the research sample.

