### Inclusion criteria

Pregnant mothers over 36 weeks or with infants in the first 6 months with a history of gestational diabetes in the last pregnancy; not having a chronic or acute disease other than gestational diabetes; willing to participate in the research and answer the questions of the questionnaire with written consent; singleton pregnancy; not having a disease whose treatment interferes with breastfeeding.

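### The behaviour outcome has no fixed infant age and the third phase has incompatible populations, so infant age at assessment is uncontrolled and the before–after behaviour comparison cannot isolate the programme

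*Protocol article*

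**What the plan says.** **Timing.** The Abstract (Methods/design, third phase) says that "breastfeeding behavior will be evaluated after delivery". The Study aim repeats this: the programme is to be implemented and the team will "evaluate the its’ effects on mothers’ breastfeeding behavior after delivery". No week, month or window appears elsewhere in the article.

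**Population of the third phase.**
- Abstract: the programme is "for 30–34 weeks pregnant mothers with gestational diabetes will be implemented during 3–4 sessions".
- Inclusion criteria (quantitative phase): "Pregnant mothers over 36 weeks or with infants in the first 6 months with a history of gestational diabetes in the last pregnancy".
- Research population: "Mothers with a history of gestational diabetes and infants up to one year".
- Exclusion criteria: women who deliver before the fourth session is finished are excluded.

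**Objectives and analysis.** One third-phase objective (printed under the heading for the qualitative-stage objectives) reads "Determining the comparison of breastfeeding behavior of women with gestational diabetes before and after the implementation". The quantitative Sample size and sampling method section assigns two health centres to each arm. The quantitative Data analysis section names an independent t-test or Mann–Whitney test between groups and a paired t-test or Wilcoxon test within groups, with no covariate.

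**The concern.** Whether and how a mother breastfeeds depends on how old the infant is. The Background treats it that way: it reports the risk of stopping in a cohort of mothers "who were examined in the first, third, sixth, and 12th months after delivery". An outcome taken at an unspecified time after birth, in women who may enter before delivery or many months after it, therefore mixes different quantities.

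Three things are at stake. The spread in infant age adds variance. The effect estimate has no stated age to which it applies. And if mean infant age happens to differ between the arms, an unadjusted test would credit that difference to the programme. Separately, the before–after objective asks for a change in a behaviour that a pregnant woman cannot yet show for this infant.

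**Working it through.** **1. Do the population statements fit together?**

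| Section | Who is in the third phase | Stage at entry |
|---|---|---|
| Abstract | women taught in 3–4 sessions | pregnant, 30–34 weeks |
| Inclusion criteria | pregnant women or mothers | over 36 weeks, or infant 0–6 months |
| Research population | mothers | infant 0–12 months |
| Exclusion criteria | those undelivered until session four ends | pregnant throughout the sessions |

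The first two rows do not overlap: a woman at 30–34 weeks is neither over 36 weeks nor a mother of an infant from this pregnancy. The exclusion in the last row makes sense only for women enrolled in pregnancy, so it conflicts with admitting women who have already delivered. No single reading satisfies all four.

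**2. What infant ages can occur at assessment?** Age at assessment is age at entry plus the time to the post-test, and that time is not given. The eligibility text alone allows a span of 6 months (Inclusion criteria) or 12 months (Research population).

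**3. Can the before–after behaviour comparison isolate the programme?**
- Enrolled in pregnancy: at pre-test there is no feeding of this infant, so there is no baseline behaviour to pair with the later value.
- Enrolled with an infant: the infant is older at post-test, so the change combines the programme with ageing, and a paired test in one arm cannot separate them.

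**4. How large could the effect be?** The article states no sample size, rate, slope or standard deviation, so there is no figure to reproduce. What follows is purely illustrative. Assumptions not in the article: a continuous score, infant age uniform over 0–6 or 0–12 months, a within-arm correlation *r* of 0.2–0.5 between score and age, 50 women per arm, a two-sided 5% test, and no clustering by centre.

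- SD of age = range/√12: 6/√12 = 1.73 months; 12/√12 = 3.46 months.
- *Noise.* Age explains r² of the variance, so the sample needed is inflated by 1/(1 − r²): 1/0.96 = 1.04 at r = 0.2, 1/0.91 = 1.10 at r = 0.3, 1/0.75 = 1.33 at r = 0.5.
- *Possible bias.* Spurious standardised difference = r × (gap in mean age)/SD(age). For r = 0.3, a 1-month gap and the 6-month span: 0.3 × 1/1.73 = 0.17. The standard error is √(2/50) = 0.20, and the chance of a significant result with no programme effect is 13.9%.

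| Gap in mean infant age (r = 0.3, 50 per arm) | 0–6 months | 0–12 months |
|---|---|---|
| 0 | 5% | 5% |
| 1 month | 13.9% | 7.2% |
| 2 months | 41.0% | 13.9% |
| 3 months | 73.8% | 25.5% |

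Over r = 0.2–0.5 and both spans, a 2-month gap gives about 9% to 82%. The result depends wholly on the gap, which the article neither states nor controls.

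**The case against.** The strongest reply has four parts.

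*An article may leave the visit date to the full protocol.* That is fair, and a missing date alone would be no finding. The contradictory populations, though, are printed text, and they are what leaves infant age open.

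*Both arms share one definition, so nothing is confounded.* This stands against the stronger reading. A reader might infer that infant age is confounded with the programme in the between-arm comparison. The article does not support that: the same criteria apply to both arms, and nothing in it makes infant age differ between centres. Imbalance is a risk with two centres per arm and no adjustment, not an established fact.

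*If the Abstract governs, all women enrol in pregnancy.* Infant age would then be set by the follow-up date and not by eligibility. That is correct, but the sections that say otherwise are the formal eligibility sections, so they cannot simply be set aside.

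*The tool is a belief questionnaire that can be answered in pregnancy.* The Tool description lists 29 attitude, 13 norm and 10 control items (29 + 13 + 10 = 52, the whole tool). A pre-test score can therefore be computed, and it would be wrong to say that no before–after comparison is possible or that only one measurement is planned, since a pre-test is mentioned. But the article names behaviour as something separate from attitude, norms, control and intention. For behaviour in that sense, the problem in step 3 remains.

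**Conclusion.** The point holds in a limited form. The third-phase populations contradict each other and the behaviour outcome has no postpartum time, so infant age at assessment is uncontrolled. The certain consequences are an effect with no defined infant age and, wherever ages do vary, added noise. Bias between the arms is possible but not shown: it is zero when mean infant ages are equal and grows with any gap. The within-arm before–after comparison of breastfeeding behaviour cannot isolate the programme for either kind of participant.

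The percentages above rest on an assumed correlation, age distribution and sample size. They ignore clustering and should not be read as this trial's error rate. The conclusion does not depend on them; it rests on the conflict between sections and on the Background's own treatment of stopping as something that happens over months.

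**What to change.** 1. Reconcile the Abstract, Research population, Inclusion criteria and Exclusion criteria into one population for the quantitative phase. Which one is the sponsor's decision.
2. Set one infant age, with a window, for the behaviour outcome, identical in both arms. The sponsor chooses the age. Enrol only women who can be assessed in that window.
3. If infant age still varies at assessment, adjust the between-arm analysis for it.
4. Base the behaviour conclusion on the between-arm comparison at that age, which the quantitative Data analysis section already provides for, and reword the before–after behaviour objective to match. Keep before–after comparison for attitude, norms, control and intention, which can be answered in pregnancy.

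The cost is mostly wording, if done before recruitment. The real downsides are that each mother must be contacted within a set window, that eligibility may narrow and slow recruitment, and that one stated objective changes. An outcome already collected at scattered ages cannot be brought to a common age afterwards; it can only be adjusted.

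### The phase-3 outcome has no fixed infant age, while eligibility spans late pregnancy to infants of 6 or 12 months, so the arms can be compared at different infant ages

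*Protocol article*

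**What the plan says.** **Outcome timing.** The abstract (Methods/design, third phase) says that "breastfeeding behavior will be evaluated after delivery". Study aim speaks of "mothers’ breastfeeding behavior after delivery", and Specific objectives has the same timing. The phase-3 objectives, listed under Specific objectives of the qualitative stage, place the comparison of behaviour and of intention before and after the intervention. No section gives a week, a month or a window.

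**Who is in phase 3.**
- Inclusion criteria (quantitative phase): "Pregnant mothers over 36 weeks or with infants in the first 6 months with a history of gestational diabetes in the last pregnancy".
- Research population: "Mothers with a history of gestational diabetes and infants up to one year are covered by comprehensive health centers".
- Abstract, Methods/design: the programme for "30–34 weeks pregnant mothers with gestational diabetes will be implemented during 3–4 sessions".
- Exclusion criteria: a birth before the fourth session has ended.

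**Arms and analysis.** Sample size and sampling method (quantitative phase) assigns two centres to each arm. Controls come from other centres and receive no intervention from the research team. Data analysis (quantitative phase) names an independent t-test or Mann–Whitney test between groups at the 0.05 level, and says that attitude, norms, perceived control, intention and behaviour will be measured and compared.

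**The concern.** The trial is about keeping up breastfeeding, which depends on time since birth. The Background makes this point itself: the cohort it relies on recorded stopping in mothers "examined in the first, third, sixth, and 12th months after delivery". A mother two weeks after birth and a mother five months after birth are not in comparable positions, yet both meet the stated timing.

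Two things are at stake. Mixing infant ages within an arm adds variation that has nothing to do with the programme. If the mix also differs between arms, part of the difference between groups reflects infant age. Older infants among controls would flatter the programme, and older infants in the intervention arm would hide a real benefit. It also stays unclear whether the result is about starting breastfeeding or maintaining it.

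**Working it through.** The protocol gives no rate, standard deviation, effect size or sample size for this outcome, so there is no figure of its own to reproduce. The check is first a reading, then an illustration.

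**Step 1: set the sections side by side.**

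| Element | Intervention arm | Control arm |
|---|---|---|
| Stage at the programme | 30–34 weeks pregnant (abstract) | no sessions |
| Birth before the fourth session | excluded | no session to count from |
| Inclusion criteria | over 36 weeks, or infant up to 6 months | same text |
| Research population | infant up to one year | same text |
| Outcome time | after birth, age not stated | same text |

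A mother who already has an infant at entry satisfies the inclusion criterion. In the intervention arm she conflicts with the exclusion, because she has given birth before any session. In the control arm nothing in the text excludes her. The written rules can therefore admit the arms at different stages. Even if every woman enrolled in pregnancy, the stated timing would not fix a common infant age.

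**Step 2: illustrate bias on a yes/no outcome (all inputs assumed).** Let both arms follow the same continuation curve S(t) = (1 − m)^t, with m the monthly cessation and no programme effect. Every intervention mother is assessed at month a and every control at month b. Then Δ = S(a) − S(b). With n per arm and p̄ the mean of the two proportions, the chance of a significant result in the programme's favour is

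Φ{ [Δ − 1.96·√(2p̄(1 − p̄)/n)] / √([p₁(1 − p₁) + p₂(1 − p₂)]/n) }.

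Example with m = 5%, a = 1, b = 3, n = 50:
- p₁ = 0.950, p₂ = 0.95³ = 0.857, Δ = 0.093.
- The two standard errors are 0.0590 and 0.0583.
- (0.0926 − 1.96 × 0.0590)/0.0583 ≈ −0.395, and Φ(−0.395) = 0.35.

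| Assessed at month (intervention vs control) | m = 3% | m = 5% | m = 10% |
|---|---|---|---|
| 1 vs 3: spurious difference | 5.7 points | 9.3 points | 17.1 points |
| 1 vs 3: significant for the programme, n = 50 | 23% | 35% | 60% |
| 1 vs 6: spurious difference | 13.7 points | 21.5 points | 36.9 points |
| 1 vs 6: significant for the programme, n = 50 | 64% | 85% | 99% |
| 1 vs 1 or 3 vs 3 | 0 points; 2.5% | 0 points; 2.5% | 0 points; 2.5% |

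The nominal rate in that one direction is 2.5%. Swapping the ages reverses the sign of the difference.

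**Step 3: illustrate bias on a score (all inputs assumed).** Let the score drift by 0.05, 0.1 or 0.2 SD per month, with a 2-month gap between arms and n = 50. The standard error is √(2/50) = 0.2 SD, so the shift is 0.5, 1 or 2 standard errors. Two-sided rejection is 8%, 17% or 52%, against a nominal 5%.

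**Step 4: noise alone.** Suppose ages are uniform over 0–6 months in both arms. The variance of age is 6²/12 = 3. With the same drifts b per month, and 1 SD as the spread at a given age, outcome variance is multiplied by 1 + 3b², that is 1.0075, 1.03 or 1.12. Over 0–12 months the variance of age is 12²/12 = 12, and the factor is 1 + 12b², that is 1.03, 1.12 or 1.48.

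Steps 2 to 4 ignore the clustering by centre, which is a separate matter.

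**The case against.** **It is an omission in a condensed article.** Visit windows and covariates are commonly left to the full protocol or the analysis plan. This stands for the covariates: an unadjusted test is not a fault on its own. It does not dispose of the point, because the article does state the timing and does state eligibility. It gives infant-age limits of 6 months and one year that disagree, and both admit mothers whom the session rules exclude.

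**Enrolment in pregnancy is implied.** The 30–34 week programme and the session-based exclusion do suggest it. If that is the intention, much of the spread in infant age disappears. But the inclusion criterion says otherwise, and a common age at assessment would still be missing.

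**No section shows an age gap between the arms.** This stands. A reader might infer that intervention mothers will be reached earlier because controls are out of the team's sight, so that an ineffective programme would look effective. The text does not support that. It says that controls receive no intervention, not that they have no contact. Participants give consent after explanations, and controls must be contacted to be measured on the same tool.

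**The tool measures beliefs.** Its 52 items are 29 + 13 + 10 on attitude, norms and perceived control, and nothing in the protocol shows that these scores drift with infant age. This also stands. The argument applies most directly to behaviour and intention, which the plan says will be compared as well.

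**Conclusion.** The point holds in a limited form. As written, the plan lets breastfeeding behaviour and intention be assessed at different infant ages, and its eligibility text does not bring both arms to the same stage. That adds noise. It biases the comparison, in either direction, only if infant age differs by arm, which the protocol permits but does not show will happen.

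No size can be read from the protocol. The figures in the working rest on assumed cessation rates, score drifts, age gaps and 50 mothers per arm. The yes/no version also uses an outcome that the described tool does not define. They show that a gap of two months could matter. They are not an estimate of this trial's false-positive rate. With no gap between arms, what remains is a loss of precision: small under the 6-month limit for the assumed drifts, larger under the one-year limit if drift is strong.

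It should be settled before recruitment. If the arms' infant ages barely overlap, adjustment afterwards cannot separate age from programme.

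**What to change.** 1. Reconcile the abstract's programme population, Research population, Inclusion criteria and Exclusion criteria so that both arms enrol at the same stage. State how the birth-before-fourth-session exclusion is applied to controls, who have no sessions. Which stage is right is for the investigators.
2. Replace the open timing with one infant age at assessment, chosen by the investigators, with a stated window and the same mode of assessment in both arms. Do this after step 1. Six months, for example, leaves no room for a mother enrolled with an infant near that age, whom the present inclusion criterion admits.
3. Record the infant's date of birth and the assessment date, so that age at assessment can be reported by arm and adjusted for.

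The cost is protocol wording and a follow-up diary. The small downside is that visits must be scheduled by birth date, and the last outcomes may come somewhat later.
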